## Abstract

**Background:**

Computed tomography is the most frequently used imaging modality in acute stroke imaging protocols. Detection of small volume infarcts in the brain and cardioembolic sources of stroke is difficult with current computed tomography protocols. Furthermore, the role of computed tomography findings to predict recurrent ischemic stroke is unclear. With ENCLOSE, we aim to improve (1) the detection of small volume infarcts with thin slice computed tomography perfusion (CTP) images and thromboembolic source with cardiac computed tomography techniques in the acute stage of ischemic stroke and (2) prediction of recurrent ischemic stroke with computed tomography-derived predictors.

Methods/design: ENCLOSE is a prospective multicenter observational cohort study, which will be conducted in three Dutch stroke centers (ClinicalTrials.gov Identifier: NCT04019483). Patients (≥18 years) with suspected acute ischemic stroke who undergo computed tomography imaging within 9 h after symptom onset are eligible. Computed tomography imaging includes non-contrast CT, CTP, and computed tomography angiography (CTA) from base of the heart to the top of the brain. Dual-energy CT data will be acquired when possible, and thin-slice CTP reconstructions will be obtained in addition to standard 5 mm CTP data. CTP data will be processed with commercially available software and locally developed model-based methods. The post-processed thin-slice CTP images will be compared to the standard CTP images and to magnetic resonance diffusion-weighted imaging performed within 48 h after admission. Detection of cardioembolic sources of stroke will be evaluated on the CTA images. Recurrence will be evaluated 90 days and two years after the index event. The added value of imaging findings to prognostic models for recurrent ischemic stroke will be evaluated.

**Conclusion:**

The aim of ENCLOSE is to improve early detection of small volume stroke and thromboembolic sources and to improve prediction of recurrence in patients with acute ischemic stroke.

## Background

Acute ischemic stroke (AIS) is a medical emergency associated with high rates of mortality and morbidity.^1^ Rapid imaging is key in the acute stroke setting as detection of ischemia and cause of the stroke is essential for treatment decisions. Currently, non-contrast computed tomography (NCCT), CT perfusion (CTP), and CT angiography (CTA) are routinely performed as part of most acute stroke imaging protocols.^2^ NCCT is used to exclude hemorrhagic stroke and to identify early signs of ischemia. CTA is required to identify the site and extent of arterial occlusion with the aim to determine eligibility for endovascular treatment (EVT). In addition, evaluation of collateral circulation on CTA helps to guide treatment strategies and predict patient outcomes.^3–5^ Important causes of stroke such as large artery atherosclerosis, dissection, or cardioembolism can also be identified with CTA. Perfusion maps generated from CTP source data may guide decision-making for intravenous thrombolysis (IVT) or EVT in the extended window and in patients with unknown time of onset of stroke (e.g. wake-up stroke) as eligibility strongly depends on infarct core and penumbra volumes.^6–8^ In addition, small perfusion defects can pinpoint more distal arterial occlusions that are difficult to detect on CTA. Also, time-invariant CTA, which is derived from the CTP source data, enables accurate assessment of the thrombus extent and the collateral status.^9^

CT imaging has certain advantages over magnetic resonance imaging (MRI) in evaluating patients with suspected AIS, such as 24/7 availability, speed, and lower costs. CTP has high sensitivity (80%) and very high specificity (95%) for infarct detection and has added value to NCCT and CTA for posterior infarct detection.^10^,^11^ However, not all clinical CT scanners have full-brain CTP coverage, which may result in false-negative findings.^10^ In addition, high noise levels and reconstructions with low spatial resolution limit the ability of CTP to identify small volume infarcts.^12^,^13^ In this study, small volume stroke was defined as a clinical diagnosis of AIS or transient ischemic attack with one of the following imaging findings: no occlusion visible on the admission CTA scan; an occlusion distal to the A2 segment of the anterior cerebral artery; an occlusion distal to the M1–M2 bifurcation of the middle cerebral artery bifurcation; an occlusion of the posterior circulation without involvement of the basilar artery.

Stroke etiology has been established as an important predictor of recurrent ischemic stroke.^14^ Thromboembolic sources of stroke include large artery atherosclerosis, dissection, and cardioembolism. In about a quarter of patients with ischemic stroke, cardioembolism is the cause of the stroke, which requires specific treatment to prevent recurrent events. The cause of the stroke remains unclear in 20–40% of the patients after routine work-up.^15–19^ An important cause of this so-called cryptogenic stroke is paroxysmal atrial fibrillation, which often remains undetected in the early stroke phase despite continuous ECG monitoring. Paroxysmal atrial fibrillation may be detected in a later phase, but the treatment-delay causes a prolonged time window of increased recurrence risk.^20^ Transthoracic echocardiography is the standard imaging modality to detect cardiac thrombus, but has limited sensitivity for this purpose depending on patient habitus and the available imaging window. Transesophageal echocardiography has a higher accuracy, but is only performed on strict indication because it is an invasive procedure, uncomfortable for the patient, and often requires light sedation. In case of delay in cardiac imaging, the culprit thrombus may have resolved. Cardiac CTA has been proposed as a fast and noninvasive alternative method for depicting cardiac thrombus.^21–23^ Non-ECG-triggered cardiac CTA can be performed in the acute stroke setting by extending the stroke CTA to include the heart with minor adjustments to the scan parameters so that the amount of contrast agent, the radiation dose, and the acquisition duration do not increase. Alternatively, ECG-triggered cardiac CTA can be performed separately in the same stroke-imaging session or soon after treatment. Cardiac CTA is performed as part of routine care in the participating centers of ENCLOSE in patients with suspected AIS. One center will use dual-energy CT, which allows for increased iodine contrast and differentiating between iodine, calcifications, slow flow, and motion artifacts. This may facilitate identification of cardiac thrombus and characterization of large artery atherosclerosis. The first goal of ENCLOSE is to improve detection of small volume infarcts and thromboembolic sources with state-of-the-art CT techniques.

The two-year recurrence rate has been estimated to be 12% in patients with AIS.^24^ Clinical prediction models have been developed for predicting recurrence, but heterogeneity is high.^25^ CT-derived predictors have been identified as prognostic for clinical outcome after AIS, but not yet for recurrences.^14^ The second goal of ENCLOSE is to prospectively evaluate the added value of CT-derived predictors for predicting recurrent ischemic stroke. If applicable, MRI-derived predictors will be evaluated additionally.

## Methods/design

### Study design

ENCLOSE (ClinicalTrials.gov Identifier: NCT04019483) is a prospective multicenter observational cohort study, which will be conducted in three Dutch stroke centers: the University Medical Center (UMC) Utrecht, the Amsterdam UMC—location Academic Medical Center (AMC) and the St. Antonius Hospital—location Nieuwegein. Patient selection, study procedures, and outcome evaluations are described in Figure 1. We will include 720 patients with suspected AIS. At presentation, patients undergo clinical evaluation, laboratory testing, and CT imaging according to local stroke protocols. The local imaging protocol for stroke includes NCCT, CTP, and CTA. Two centers will perform non-ECG-triggered CTA from the base of the heart up to the top of the head; one center will perform a non-ECG-triggered CTA from the aortic arch to the head and a separate ECG-triggered cardiac CTA. Patients with a suspected small volume infarct will be asked to undergo an additional brain-MRI within 48 h after hospital admission. The included patients will be followed for two years to identify recurrent ischemic strokes and to evaluate 90-day clinical outcome.

**Figure 1. fig1-2396987320966420:**
[figure not shown]
Flowchart of patient selection, study procedures, and outcome evaluations. Distal occlusion on admission CTA is defined as an occlusion distal to the A2 segment of the anterior cerebral artery, distal to the M1–M2 bifurcation of the middle cerebral artery, or an occlusion of the posterior circulation excluding basilar and vertebral artery occlusions. CT: computed tomography; MRI: magnetic resonance imaging; A2: A2 segment of anterior cerebral artery; M1–M2: junction between M1 and M2 segments of the middle cerebral artery; CTA: computed tomography angiography; FLAIR: fluid-attenuated inversion recovery; DWI: diffusion-weighted imaging; MRA: magnetic resonance angiography; SNAP: simultaneous non-contrast angiography and intraplaque hemorrhage.

### Inclusion and exclusion criteria

Patients will be included if the following criteria are met: age of 18 years or older, time from symptom onset, or last seen well until admission CT is less than 9 h,^26^ clinical diagnosis of AIS or transient ischemic attack (TIA), and informed consent from patient or legal representative. Patients who awake with stroke symptoms can only be included if they went to sleep without any stroke symptoms, and the time from going to sleep until imaging is less than 9 h. To participate in the MRI-part of this study, the patient also has to meet the following criteria: no occlusion visible on the admission of CTA scan or an occlusion distal to the A2 segment of the anterior cerebral artery, distal to the M1–M2 bifurcation of the middle cerebral artery bifurcation or an occlusion of the posterior circulation without involvement of the basilar artery, and no contraindications for undergoing MRI. Patients with another diagnosis such as intracerebral hemorrhage, subarachnoid hemorrhage or tumor, or patients with known contrast allergy or renal failure will be excluded from the study.

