### Statistical analysis

#### Ischemia detection

##### Sample size

Over 30,000 people suffer from an ischemic stroke in the Netherlands each year.^31^ About 30% of them will have an intracranial large artery occlusion, and 70% will have a minor stroke or TIA. As a result, 500 of the 720 subjects are possible candidates for small volume infarct detection. Assuming that at least half of the 500 patients will give informed consent for the extra follow-up MRI and do not have contra-indications for undergoing MRI, we should have 250 potential patients for the part of the study that concerns small volume stroke detection. Based on the historical cohort (Dutch Acute Stroke Study: 2009–2013, METC number 08–373), we expect to improve the sensitivity of CTP for small volume stroke detection from 0.45 to at least 0.75, which approaches the sensitivity of MRI (0.88–1.00).^32^ With a minimal acceptable lower 95% confidence level of 0.6 for the increased sensitivity, we will need about 107 MRI subjects.^33^ We expect that about 60% of patients with suspected stroke, and no large artery occlusion on admission will have an infarct on follow-up imaging.^34^ This means that we need to include at least 178 patients for the MRI part of this study.

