## Discussion

CTP has good sensitivity (80%) and specificity (95%) for brain infarct detection.^10^,^11^ However, accurate detection of small volume infarcts is still difficult with CTP because of noise and limited spatial resolution.^38^ In addition, evaluation of the posterior fossa is often hampered by streak artefacts.^39^ In case no stroke is visualized with CT, an MRI is sometimes indicated to ascertain the diagnosis. By improving the detection of small volume stroke by CTP, additional MRI may become unnecessary in the diagnostic pathway, and early detection of these small ischemic strokes may influence acute treatment decisions.

Cardiac CTA may be a fast and noninvasive method for depicting cardiac thrombus in the acute stroke phase. It has some advantages over (delayed) echocardiographic imaging and may facilitate in starting anticoagulant treatment in time. Adding cardiac CTA to the standard stroke imaging protocol will cost an additional 2 s, and the additional radiation exposure will be marginal.

Prediction of recurrences has been subject of multiple studies.^25^ However, developed clinical models for long-term prediction have limited discriminative ability with c-statistics not greater than 0.7.^25^ Addition of imaging predictors to clinical models may improve their predictive value.

For this study, we will not exclude particular subgroups of patients with AIS for reasons of clinical applicability and generalizability. We select on acquisition timing as CT findings such as ischemia may differ between patients who present in an early time window when compared with patients who present in a late time window. Different kinds of CT scanners will be used as multiple centers are involved in this study. Although this can lead to heterogeneity of imaging acquisitions, it enables generalization of the results to other stroke centers.

In conclusion, the ENCLOSE study aims to increase the diagnostic accuracy of CTP for detection of small volume infarcts and diagnostic yield of CTA for cardioembolic sources. Besides, the study aims to improve prognostic models for predicting recurrent ischemic stroke. CT-derived predictors, including predictors derived from early cardiac CTA, will be used to improve prognostication of recurrent ischemic stroke.

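### Eligibility is set on a diagnosis of AIS or TIA with no time point, while the cohort and infarct rate are for suspected stroke; DWI-negative mimics can be removed, so specificity, NPV and ROC results may be biased or may not transfer

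*Protocol article*

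**What the plan says.** The protocol article describes two populations.

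- **Suspected stroke.** The abstract states: "Patients (≥18 years) with suspected acute ischemic stroke who undergo computed tomography imaging within 9 h after symptom onset are eligible". Study design states: "We will include 720 patients with suspected AIS". Under Ischemia detection, Sample size, the step from infarcts to MRI patients uses this rate: "We expect that about 60% of patients with suspected stroke, and no large artery occlusion on admission will have an infarct on follow-up imaging".
- **Diagnosed AIS or TIA.** Inclusion and exclusion criteria require "clinical diagnosis of AIS or transient ischemic attack (TIA), and informed consent from patient or legal representative". The Background section agrees with this: "small volume stroke was defined as a clinical diagnosis of AIS or transient ischemic attack with one of the following imaging findings".

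The criteria also exclude "Patients with another diagnosis such as intracerebral hemorrhage, subarachnoid hemorrhage or tumor". The examples illustrate an open class. Nothing says whether the admission working diagnosis or a later one decides, and the MRI part has no separate rule on this point.

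Diagnostic value plans sensitivity, specificity, PPV, NPV and ROC curves against DWI, with superior sensitivity as the hypothesis. The Discussion says that MRI is sometimes needed to settle the diagnosis when CT shows no stroke, and hopes that with better CTP "additional MRI may become unnecessary in the diagnostic pathway".

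**The concern.** Take a patient with suspected stroke, no occlusion on CTA, a negative DWI within the 48-hour window and a later conclusion that the event was a mimic. Under the criteria as worded, this patient now has another diagnosis and may be excluded. A patient with an infarct on DWI would ordinarily not be. Eligibility can therefore depend on the reference standard, and also on CTP if CTP helped to form the diagnosis.

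Other parts of the article make this possible in practice. MR imaging allows a routine-care MRI within 48 h to serve as the study scan, and the Discussion says that such an MRI may be done to establish the diagnosis. One scan can thus both decide the diagnosis and be the reference. Ethical considerations provides for patients who die before consent is obtained, so enrolment may be completed after the acute imaging.

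The measures at stake are those that depend on DWI-negative patients: specificity, NPV and the ROC curves. Sparing MRI after a negative CT depends mainly on NPV, and that decision is taken before mimics have been sorted out.

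**Working it through.** **Inputs.** Sensitivity 0.75, lower limit 0.60, 107 infarcts, 60% prevalence and 178 patients come from Ischemia detection, Sample size. Specificity 0.95 is the general CTP figure in the Background and Discussion. It is not specific to small infarcts and serves only as illustration. The share of mimics is not given, so a range is assumed.

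**The plan's own figures.** With an exact binomial calculation, 107 is the smallest n for which a one-sided 95% lower limit exceeds 0.60 with probability at least 0.95 when true sensitivity is 0.75 (at least 73 of 107 detected; probability 0.955). The article does not state the one-sided limit or the 0.95 probability; they are the reading that reproduces its figure. Then 107 / 0.60 = 178.3, given as 178.

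**Dropping DWI-negative patients.** Let d be the fraction of DWI-negatives removed as mimics, regardless of CTP result, and let the 60% include mimics.

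- Prevalence: p = 0.6 / [0.6 + 0.4(1 − d)]
- NPV = 0.95(1 − p) / [0.95(1 − p) + 0.25p]
- Patients needed for 107 infarcts: 107 / p
- DWI-negatives among 178: 178(1 − p)

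| d | p | NPV | Needed for 107 infarcts | DWI-negatives in 178 |
|---|---|---|---|---|
| 0 | 0.600 | 0.380/0.530 = 0.72 | 179 | 71 |
| 0.25 | 0.667 | 0.655, i.e. 0.66 | 161 | 59 |
| 0.50 | 0.750 | 0.559, i.e. 0.56 | 143 | 45 |

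Since 40% of patients are DWI-negative, d = 0.25 and 0.50 mean that 10% and 20% of all suspected-stroke patients are mimics. PPV moves little: 0.96, 0.97 and 0.98.

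**Selective removal.** Suppose DWI-negative patients with a CTP deficit stay in as TIA, and only those with a normal CTP are relabelled as mimics. Of 100 DWI-negatives, 95 are true negatives. Removing k of them gives specificity (95 − k)/(100 − k):

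- k = 20: 75/80 = 0.94
- k = 40: 55/60 = 0.92

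**The other reading of the 60%.** If the 60% already refers to AIS or TIA only, the planned cohort has NPV 0.72. With mimics forming 10% or 20% of suspected stroke, prevalence in that wider group is 0.6 × 0.9 = 0.54 or 0.6 × 0.8 = 0.48, and NPV is 0.76 or 0.81. On either reading, the NPV from a cohort without mimics is lower than that in suspected stroke.

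**The case against.** The strongest reply is that removal after DWI is nowhere stated. The criteria speak of a clinical diagnosis, not a final one. Study design asks patients with a suspected small infarct to have MRI, and MR imaging scans those who already meet the selection criteria, so selection seems to come first. Hemorrhage is excluded on the admission non-contrast CT, and contrast allergy and renal failure, in the same sentence, are pre-existing conditions. The sample size allows for about 40% of MRI patients without an infarct. The flowchart in Figure 1, which is not shown, or the full protocol may fix the time point.

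Much of this stands. A reader might infer that mimics do drop out; the article only permits it. A reader might infer that specificity and NPV are meaningless. They are not: TIA and DWI-negative stroke remain eligible, so both can be estimated for diagnosed AIS or TIA. A reader might also infer that the whole sample size was built for suspected stroke. Only the 60% step was; the pool of 500 out of 720 comes from ischemic stroke patients. The direction is cautious too, since a cohort without mimics understates NPV, and the hope of sparing MRI is one tentative sentence in the Discussion.

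The reply does not remove the contradiction. The abstract and the criteria name different eligible populations in print, and nothing in the exclusion requires the diagnosis to precede DWI.

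**Conclusion.** The point holds as a conflict over the target population that leaves room for reference-dependent exclusion. It is not a demonstrated bias. The specificity, NPV and ROC results may be biased and may not carry over to suspected stroke.

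On the assumed shares, NPV moves from 0.72 to 0.66 or 0.56. Specificity falls from 0.95 to 0.94 or 0.92 only if every patient removed had a normal CTP. These figures rest on an unknown mimic share, on a general CTP specificity and, for the NPV range, on the 60% including mimics.

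The sensitivity hypothesis is unaffected, because sensitivity is calculated in DWI-positive patients. If mimics leave, 178 is more than enough for 107 infarcts. The point should be corrected because patients excluded and not recorded cannot be restored in the analysis.

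**What to change.** Separate eligibility by objective.

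- **Ischemia detection:** set eligibility on the working diagnosis at admission CT (suspected AIS or TIA, with hemorrhage or tumor excluded on that CT). Keep every patient who has both CTP and DWI in the diagnostic analysis, whatever the final diagnosis.
- **Recurrence model:** apply the requirement of a final diagnosis of AIS or TIA here only.
- **Wording:** use one description of the population in the abstract, Study design and the criteria, and state that the 60% infarct rate refers to it.

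The cost is rewording of one criterion and of the analysis-set definition, with no extra scans. The downside is a more mixed DWI-negative group.

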### Baseline data

#### Clinical data

The following baseline characteristics will be collected: age, sex, time of symptom onset or last seen well in case of a wake-up stroke or other strokes with unknown time of onset, National Institutes of Health Stroke Scale (NIHSS), and the Trial of Org 10172 in Acute Stroke Treatment (TOAST) classification. The following cardiovascular risk factors will be recorded: history of stroke, coronary heart disease, atrial fibrillation, congestive heart failure, valvular disease, peripheral vascular disease, active cancer, hypertension, dyslipidemia, diabetes mellitus, smoking, and medication use. Biometry data include length and weight. Furthermore, therapeutic interventions such as intravenous administration of tissue-type plasminogen activator (tPA), endovascular stroke treatment, and carotid endarterectomy will be recorded. Laboratory data include levels of hemoglobin, thrombocytes, glucose, HbA1c, creatinine, C-reactive protein, lipids, and international normalized ratio. Medication use on hospital discharge will be collected as well.

#### CT imaging

##### Acquisition

Patients with suspected ischemic stroke will undergo NCCT, CTP, and CTA. One institution will use a dual-energy CT scanner as part of standard care. The local stroke imaging protocols from the three participating hospitals will be used. Contrast and flow parameters for CTP and CTA are shown in Table 1. The acquisition and reconstruction parameters for the different CT scanners are shown in Tables 2 and 3.

**Table 1. table1-2396987320966420:** Contrast parameters for CT perfusion and CT angiography acquisition.

Center	Scanner	Contrast	CTP				CTA			
			Bolus (ml)	Flow (ml/s)	Saline (ml)	Flow (ml/s)	Bolus (ml)	Flow (ml/s)	Saline (ml)	Flow (ml/s)
UMC Utrecht	Philips Brilliance iCT-256	Ultravist-300 mg/ml	40	6	40	6	65	6	40	6
	Philips IQon spectral CT	Ultravist-300 mg/ml	50	6	40	6	65	6	40	6
Amsterdam UMC	Siemens Force	Iomeron 300 mg/ml	35	6	40	6	50	6	40	6
	Siemens AS+	Iomeron 300 mg/ml	35	6	40	6	50	6	40	6
St. Antonius Hospital	64-Brilliance	Xenetix 300 mg/ml	40	5	50	4	55	4	40	4
	256-Brilliance iCT Philips	Xenetix 300 mg/ml	40	5	50	4	55	4	40	4

**Table 2. table2-2396987320966420:** Acquisition and reconstruction parameters of the CT perfusion stroke protocols in the participating centers.

Center	Scanner	Scan type	Peak voltage (kVp)	Exposure (mAs)	Beam collimation (mm)	Slice thickness/increment (mm)	Reconstruction (level), kernel	Matrix
UMC Utrecht	Philips Brilliance iCT-256	Axial	80	150	128 × 0.625	5.0/5.0 of 1.0/0.8	iDose (5), UB	512 × 512
	Philips IQon spectral CT	Jog Mode	120	35	64 × 0.625	5.0/5.0 of 0.9/0.7	iDose (5), UB	512 × 512
Amsterdam UMC	Siemens Force	Axial	80	84	192 × 0.6	1.0/0.7	Admire (1), Bv36	512 × 512
	Siemens AS+	Axial	80	200	32 × 0.6	5.0/5.9	Saffire (1), H20f	512 × 512
St. Antonius Hospital	64-Brilliance	Axial	80	125	64 × 0.625	5.0/5.288	iDose (3), B	512 × 512
	256-Brilliance iCT Philips	Axial	80	125	128 × 0.625	5.0/5.0	iDose (5), B	512 × 512

**Table 3. table3-2396987320966420:** Acquisition and reconstruction parameters of the CT angiography stroke protocols in the participating centers.

Center	Scanner	Scan type	Peak voltage (kVp)	Exposure (mAs)	Pitch	Beam collimation (mm)	Slice thickness/increment (mm)	Reconstruction (level), kernel	Matrix
UMC Utrecht	Philips Brilliance iCT-256	Helical	100	AEC	0.914	128 × 0.625	3.0/3.0 or 0.9/0.45	iDose (3), B	512 × 512
	Philips IQon spectral CT	Helical	120	AEC	0.609	64 × 0.625	5.0/5.0 or 0.9/0.7	iDose (5), B	512 × 512
Amsterdam UMC	Siemens Force	Helical	100	200	0.55	192 × 0.6	1.0/0.7	Admire (1), Bv36	512 × 512
	Siemens AS+	Helical	100	200	0.55	128 × 0.6	1.0/1.0	Saffire (1), I46f	512 × 512
St. Antonius Hospital	64-Brilliance	Helical	100	230	1.033	64 × 0.625	2.0/1.5	iDose (3), B	512 × 512
	256-Brilliance iCT Philips	Helical	100	230	0.763	128 × 0.625	2.0/1.5	iDose (3), B	512 × 512

AEC means automatic exposure control.

